#### 2.4.5. Step 5: Final Consensus or Dissensus

Panel statements will be created based on the summary of the results of the last stable round. The panellists will be able to comment on the final survey results, consensus statements, and the article before publishing.

### 2.6. Analysis Plan

A descriptive analysis of each survey round will be performed. The stability of the responses will be analyzed from the second round onwards using the non-parametric Chi-square test or Kruskal–Wallis test. To define the stability of statements, a *p*-value of ≥0.05 will be interpreted as a lack of stability. Consensus will be defined when a choice in the MCQ or Likert-scale question has at least 75% of the votes from panellists. For the Likert-scale, the answering options are divided into disagreement (1 to 3), neutral (4), and agreement (5 to 7): 1 for strongly disagree, 2 for somewhat disagree, 3 for disagree, 4 for neutral, 5 for somewhat agree, 6 for agree, and 7 for strongly agree. Stability is assessed after two consecutive rounds of answers defined as consensus or dissensus. All data will be analyzed, regardless of the completeness of answers.

The steering committee will compile the results from each Delphi round and share them with the panellists, together with the survey of the following round. These results will demonstrate the degree of consensus or dissensus achieved for each statement. In the final results, percentages of voting for each answering option will be reported.

The findings from this study will be presented in two separate reports: (1) Humidification and Nebulization, and (2) Suctioning and Mucus mobilization techniques.

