## Abstract

Intubated critically ill patients are susceptible to secretion accumulation because of compromised airway clearance. Various airway clearance interventions are employed to prevent complications arising from mucus retention. This Delphi study aims to collect global opinions in an international expert panel of ICU professionals on the usefulness of these various airway clearance interventions. A steering committee performed a literature search informing the formulation of statements. Statements are grouped into two distinct parts: (1) Humidification and Nebulization, and (2) Suctioning and Mucus mobilization techniques. For each part, a diverse panel of 30–40 experts will be selected, with concerted effort to involve experts from various medical specialties involved in airway clearance methods. Multiple choice questions (MCQs) or 7-point Likert-scale statements will be used in the iterative Delphi rounds to reach consensus on various airway clearance interventions. Rounds will continue until stability is achieved for all statements. Consensus will be deemed achieved when a choice in MCQs or a Likert-scale statement achieves ≥75% agreement or disagreement. Starting from the second round of the Delphi process, stability will be assessed using non-parametric χ^2^ tests or Kruskal–Wallis tests. Stability will be defined by a *p*-value of ≥0.05.

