### 2.3. Expert Panel

An international expert panel of at least 35 to 40 healthcare professionals representing ICU-nurses, respiratory therapists (or comparable versions, based on local implementation), physiotherapists, speech and language therapists, ICU-physicians, and pulmonologists with expertise in the field of invasively ventilated ICU-patients will be selected based on the following criteria:○At least 5 years of clinical experience, with care for invasively ventilated patients (teaching and non-teaching);○Participation in the development of a guideline or authorship of at least one paper on airway care for invasive ventilated patients in an international peer-reviewed journal;○No more than 70% of the panellists from each sex, and from each of the high-, low-, and middle-income countries;○Has a good command of the English language.

Purposive sampling will be utilized to recruit panellists by reviewing recent publications in the field of airway care for invasive ventilated patients. Selection of panellists will be guided by predefined criteria, with deliberate efforts to ensure a balance in gender and geographical representation. Panellists will receive an invitation in English via email detailing their role, the study’s objectives, and the Delphi process. Those who accept the invitation will participate in the Delphi rounds, with ongoing communication and regular progress updates provided to encourage their continued involvement. These updates will be provided in Delphi round reports after each round. To minimize dropout rates, at least three reminder emails will be sent during each round, and any feedback or concerns regarding the process will be addressed. Additionally, a schedule of Delphi rounds (each lasting 2 weeks) will be adhered to in order to maintain continuity.

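### The stability test in Section 2.6 treats repeated answers from the same 30–40 panellists as independent samples, so under the Abstract's rule real shifts are too easily called stable

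*Protocol article*

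**What the plan says.** Section 2.6 (Analysis Plan): "The stability of the responses will be analyzed from the second round onwards using the non-parametric Chi-square test", with Kruskal–Wallis as the alternative. It does not say which test serves which type of item. Consensus requires that one choice "has at least 75% of the votes from panellists", and Likert answers are pooled into disagree, neutral and agree.

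The panel is small. The Abstract states "For each part, a diverse panel of 30–40 experts will be selected", while Section 2.3 has "An international expert panel of at least 35 to 40 healthcare professionals". Section 2.3 also makes clear that those who accept the invitation take part in the successive rounds, so the same people answer repeatedly.

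The p-value rule appears twice, in opposite directions. The Abstract says "Stability will be defined by a *p*-value of ≥0.05"; Section 2.6 says "a *p*-value of ≥0.05 will be interpreted as a lack of stability".

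Under Sections 2.4.4 and 2.4.5, rounds continue until every statement is stable, and the panel statements are drawn from the last stable round.

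**The concern.** A chi-square test on a rounds-by-answers table assumes that the two rows come from different people. Here they come from the same people, many of whom can be expected to repeat their answer. The change between rounds then varies much less than the test supposes, and the p-value is too large.

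If p≥0.05 closes a statement as stable, a p-value that is too large ends the process while opinion is still moving. Small panels with one dominant answer add a second, lesser problem: with many options the remaining cells are sparse, and the large-sample p-value becomes more conservative again. At stake is whether a published stable consensus was in fact stable.

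**Working it through.** The article gives no error rate or power for the stability test, so there is no figure of its own to reproduce.

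**Inputs.** From the documents: n=30 to 40 (Abstract), the 75% consensus threshold and three Likert groups (2.6), and the same panellists in each round (2.3). Assumed: the number of MCQ options (not stated), the size of the shift, and the share r of panellists who repeat their answer.

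**Step 1: effect of pairing when nothing changes.** Suppose a share r repeat their answer and the rest answer afresh from the same distribution. The between-round change in a proportion p then has variance 2p(1−p)(1−r)/n, while the test assumes 2p(1−p)/n. The statistic behaves roughly like (1−r) times a chi-square variable, so the true rejection rate is P(χ² > c/(1−r)), where c is the nominal critical value.
- r=0.5, two groups: 3.84/0.5 = 7.68, rate 0.0056.
- r=0.5, three groups: 5.99/0.5 = 11.98, rate exp(−5.99) = 0.0025.

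Simulation at n=35 with 75% on one answer gives 0.0056 and 0.0034. With r=0 it gives 0.046 and 0.047, and with r=0.7 it is below 0.001 for three groups. The nominal rate is 0.05.

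**Step 2: a hand check with a real shift.** Support falls from 80% to 60% because panellists leave the majority answer, and nobody else moves. With equal n the statistic is Σ(a−b)²/(a+b).
- n=30, three groups, 24/3/3 then 18/6/6: 36/42 + 9/9 + 9/9 = 2.86 on 2 df, p = exp(−1.43) = 0.24. Six panellists changed, giving 2⁶ = 64 swap patterns. Only the two that keep all six together reach the observed value, so the within-panellist p = 2/64 = 0.031.
- n=40, three groups, 32/4/4 then 24/8/8: 64/56 + 16/12 + 16/12 = 3.81, p = exp(−1.905) = 0.15. Within-panellist p = 2/2⁸ = 0.008.
- n=40, five options, 32/2/2/2/2 then 24/4/4/4/4: 64/56 + 4×(4/6) = 3.81 on 4 df, p = exp(−1.905)×(1+1.905) = 0.43. Within-panellist p is again 0.008.

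In each case a one-way move across the 75% line gives chi-square p≥0.05.

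**Step 3: detection rates by simulation.** Panellists on the majority answer leave at random (0.80×0.75 = 0.60; 0.95×0.80 = 0.76). They spread evenly over the other answers, and everyone else repeats.

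| Shift | Groups | n | Planned chi-square | Within-panellist permutation |
|---|---|---|---|---|
| 80% to 60% | 3 | 30, 40 | 13%, 27% | 57%, 83% |
| 80% to 60% | 5 | 30, 40 | 2%, 8% | 59%, 85% |
| 95% to 76% | 3 | 30, 35, 40 | 32%, 43%, 57% | 51%, 67%, 80% |
| 95% to 76% | 5 | 30, 35, 40 | 11%, 18%, 27% | 50%, 70%, 82% |

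Repeating the 80%-to-60% runs moves the figures by about two percentage points at most. With no true change, the permutation test rejects in at most about 3% of runs.

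**Step 4: how much is due to small cells alone.** With 75% on one of k answers, each other cell expects 0.25n/(k−1). That is 3.75 to 5.0 for three groups and 1.9 to 2.5 for five options (n=30 to 40). The true size of the chi-square test, with rounds treated as independent (nominal 0.05), is:

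| Answers | 75% support, n=30 / 40 | 90% support, n=30 / 40 |
|---|---|---|
| 3 | 0.044 / 0.054 | 0.022 / 0.030 |
| 4 | 0.040 / 0.044 | not run |
| 5 | 0.026 / 0.036 | not run |
| 7 | 0.014 / 0.019 | 0.002 / 0.002 |

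An unpaired exact p-value barely helps. For 75% to 55% at n=30, power goes from 0.29 to 0.28 with three groups and from 0.20 to 0.23 with five.

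**The case against.** **The direction of harm.** Section 2.6, the section that defines the test, reads p≥0.05 as lack of stability. On that wording an inflated p-value keeps statements open rather than closing them. This stands: the harm follows only under the Abstract's rule. Section 2.6 taken literally would, however, call identical answers in two rounds unstable, so the Abstract's direction is the workable one.

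**Level of detail.** An article may leave exact versus large-sample computation to an analysis plan that is not shown. That is fair for the small-cell part. It does not answer the pairing point, because independence is built into the test that the article names. Kruskal–Wallis, the alternative, also assumes independent groups.

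**Which statements are tested.** One sentence in 2.6 may confine the stability assessment to statements classed as consensus or dissensus in both rounds, which could exclude a fall to 60%. The 95%-to-76% rows stay above 75% throughout and show the same loss. There the consensus label would not change, only the stability label.

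**Other safeguards.** Section 2.4.4 also requires that no more than 10% of panellists give feedback needing adjustment, and 2.6 promises percentages for every option. Both help the reader, but neither tests whether votes moved.

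**A stronger reading.** A reader might infer from expected counts below 5 that the chi-square p-value fails for every statement near 75% support, and that an exact test cures it. The documents and the figures do not support this. With two to four categories, including pooled Likert items, the size at 75% support is close to nominal. The clear small-cell effect needs about five or more options, a number the article does not give, or near-unanimity.

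**Conclusion.** The point holds in this form: the planned stability test ignores that the same panellists answer each round and is therefore strongly conservative. For an 80%-to-60% shift its detection is about 13% to 27% with three groups and 2% to 8% with five options, against 57% to 85% for a paired permutation test. Sparse cells are a secondary cause, limited to MCQs with many options and near-unanimous items.

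The sizes rest on an assumed number of options, shifts made up of panellists leaving the majority answer, and the rest repeating their vote. More movement in both directions would narrow the gap. The conclusion that shifts are called stable rests on the Abstract's rule and cannot be drawn from Section 2.6 as worded.

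**What to change.** 1. Reconcile the Abstract and Section 2.6 on what p≥0.05 means. The rest depends on this.
2. In 2.6, replace the unpaired chi-square p-value with a permutation p-value of the same statistic. Obtain it by swapping each panellist's own answers between the two consecutive rounds, among panellists who answered both. Section 2.1 says responses are not anonymous to the coordinating members, so linking is feasible; the anonymity promised in 2.4.3 can be kept between panellists.
3. Where answers cannot be linked, an unpaired exact test is only a fallback. It deals with sparse cells but leaves the pairing problem in place.

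The cost is a sentence or two in 2.6 and a few lines of code, with no new data. Section 2.8 indicates that the first round has not yet started. The downside is that some statements may go to a further round. Non-significance in a panel of 30–40 also remains weak evidence of stability: even the better test misses roughly 15% to 43% of the 80%-to-60% shifts (100% minus 85% and 57%).

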#### 2.4.4. Step 4: Subsequent Delphi Rounds

The steering committee will evaluate the results of each round through online meetings. Statements will be revised, removed, or added as necessary, based on the feedback, comments, and responses received by the panel, The revised and remaining statements will be continued through subsequent rounds until a stable consensus or dissensus is reached (defined as ≥75% agreement or disagreement on a Likert scale and selected options in an MCQ). A summary of the results from each round will be shared with the panellists, and the survey process will be repeated using the updated questionnaire. The Delphi rounds will continue until the responses stabilize, with no more than 10% of panellists providing feedback that requires further adjustments. The process will be repeated until stability is achieved for all statements.

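### Section 2.6 reverses the stability rule: it treats p ≥ 0.05 between rounds as instability, where the Abstract treats the same result as stability

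*Protocol article*

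**What the plan says.** The article states the stability rule twice.

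- **Abstract:** "stability will be assessed using non-parametric χ^2^ tests or Kruskal–Wallis tests", starting from the second round, followed by "Stability will be defined by a *p*-value of ≥0.05".
- **Section 2.6 (Analysis Plan):** stability is analysed "from the second round onwards using the non-parametric Chi-square test or Kruskal–Wallis test", and a p-value "value of ≥0.05 will be interpreted as a lack of stability".

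Two other sections depend on the result. Section 2.4.4 makes stability a condition for ending the rounds: "The process will be repeated until stability is achieved for all statements". Section 2.4.5 uses it to choose the source of the output: "Panel statements will be created based on the summary of the results of the last stable round". Section 2.6 adds a condition on timing: "Stability is assessed after two consecutive rounds of answers defined as consensus or dissensus".

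No other section says which of the two rules governs.

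**The concern.** The tests, the threshold and the starting round are the same in both places, but the conclusions drawn from the p-value are opposite. Any between-round result is therefore stable under one statement and unstable under the other.

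An analyst would normally work from the Analysis Plan, and that is the version that runs against the logic of the tests. If it were followed, settled statements would go on failing the stability condition while statements still in motion would pass it. Since both rules are published, either classification could later be presented as the prespecified one.

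**Working it through.** There is no sample size or power figure to reproduce on this point. The check concerns the direction of the rule and what each version does.

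**Inputs from the article.** The tests are chi-square or Kruskal–Wallis and the threshold is 0.05. Likert answers are grouped as disagree (1–3), neutral (4) and agree (5–7) (section 2.6). Panel size is 30–40 per part (Abstract); section 2.3 says at least 35 to 40. I used n = 30, 35 and 40.

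**Step 1: direction.** Used to compare rounds, both tests have equal response distributions as the null hypothesis. A small p-value is evidence of change; a large one is no evidence of change.

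**Step 2: identical answers.** With 7 disagree, 7 neutral and 21 agree in both rounds, observed equals expected in every cell, so chi-square = 0 and p = 1. Kruskal–Wallis on identical 7-point ratings also gives p = 1. The Abstract calls this stable; section 2.6 calls it unstable.

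**Step 3: a clear shift, n = 35.** Round A: 10 disagree, 7 neutral, 18 agree. Round B: 2, 1, 32. The expected counts per round are the averages 6, 4 and 25.

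Chi-square = 2 × (4²/6 + 3²/4 + 7²/25) = 2 × (2.667 + 2.25 + 1.96) = 13.75 on 2 df, so p = exp(−13.75/2) ≈ 0.001.

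Section 2.6 would call this stable. One expected count per round is below 5. Collapsing to agree versus not agree (18/17 against 32/3, expected 25/10) gives 2 × (7²/25 + 7²/10) = 13.72 on 1 df, p about 0.0002, so the conclusion does not depend on the sparse cells.

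**Step 4: a shift with both rounds above 75%.** Agreement moves from 27/35 (77%) to 35/35. Expected counts are 31 agree and 4 not agree per round. Chi-square = 2 × (4²/31 + 4²/4) = 9.03 on 1 df, p about 0.003. This pair too would be stable under section 2.6.

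**Step 5: how often, by simulation.** There were 4,000 replicates per setting, with rounds drawn as independent samples. The article gives no response distributions, so these are assumptions: probabilities 0.05, 0.05, 0.10, 0.20, 0.20, 0.25, 0.15 over the seven points (60% agreement), and after a large shift 0.01, 0.01, 0.03, 0.05, 0.15, 0.35, 0.40 (90% agreement).

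| Situation | Test | n = 30 | n = 35 | n = 40 |
|---|---|---|---|---|
| Opinion unchanged: p ≥ 0.05 (unstable under 2.6) | Kruskal–Wallis | 94.4% | 94.8% | 95.3% |
| Opinion unchanged: p ≥ 0.05 (unstable under 2.6) | Chi-square, 3 groups | 95.2% | 94.9% | 95.1% |
| Large shift: p < 0.05 (stable under 2.6) | Kruskal–Wallis | 89% | 92% | 95% |
| Large shift: p < 0.05 (stable under 2.6) | Chi-square, 3 groups | 69% | 76% | 83% |

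The same panellists answer each round, so their ratings are correlated and a test that ignores this rejects less often. With an assumed between-round correlation of 0.5–0.8 and no true shift (2,500 replicates), Kruskal–Wallis gave p < 0.05 in 0.0–1.2% of replicates. Section 2.6 would then label 98.8–100% of unchanged statements unstable.

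**The case against.** **Section 2.6 may be coherent under another test.** If the chi-square test were one of association between each panellist's linked answers in two rounds, a small p-value would indicate consistency. Section 2.1 says responses are not anonymous to the coordinating members, so linkage is possible. But section 2.6 describes no such test, the reading does not fit Kruskal–Wallis comparing rounds, and the Abstract contradicts it. It leaves the contradiction in place.

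**It is probably a drafting slip.** The Abstract has the usual direction, and the steering committee includes two Delphi methodologists. That makes literal application less likely. It is no reason to leave opposite rules in print.

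**The consequences are easily overstated.** A reader might infer that section 2.6 would by itself close shifting statements, or that the final recommendations would rest on the least settled answers. The article does not support this. Section 2.4.4 also requires a stable result of at least 75% and no more than 10% of panellists giving feedback that needs adjustment, and section 2.6 ties the assessment to two consecutive rounds of consensus or dissensus. On a narrow reading of that last condition, the 18/35 to 32/35 pair might not be assessed at all, because 18/35 is 51%; the 27/35 to 35/35 pair would be. Nor can a count of statements closing per round be given, since the article states neither the number of statements nor how many will move.

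This objection stands as a limit on the claim: a shifted statement would meet the stability condition, which is not the same as being closed.

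**Conclusion.** The point holds and should be corrected before the first round. The two rules are exact opposites for the same tests, and under the ordinary between-round comparison section 2.6 is the reversed one. That conclusion rests only on the null hypothesis of the named tests and on the p = 1 result for identical answers.

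If section 2.6 were followed literally, about 95% of unchanged statements would fail the stability condition at each comparison with independent rounds, and 98.8–100% under the assumed correlations. Large shifts would meet it in roughly 69–95% of comparisons, depending on the test, the panel size and the assumed distributions. Both the ending of rounds and the choice of the last stable round would be misdirected, within the limits set by the 75% and 10% criteria.

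A reader might also conclude that the Abstract's rule is itself inadequate, because a non-significant p-value with 30–40 panellists is weak evidence of stability. That is a separate question about the choice of test. It does not bear on the direction of the rule.

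**What to change.** In section 2.6, replace the sentence on the p-value with, for example: *A between-round p-value <0.05 will be interpreted as a lack of stability; p ≥0.05 will be interpreted as stability.* This matches the Abstract and leaves the stopping rule fully defined. Section 2.4.4 states no p-value rule, so it needs no change on this point.

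The cost is one sentence. Section 2.8 places the first round in the future, so on the article's own account the correction would come before any responses are collected.

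### Section 2.6 transposes the labels of Likert codes 2 and 3: consensus is unaffected, but a Kruskal–Wallis test on the seven codes would mis-rank two answers

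*Protocol article*

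**What the plan says.** Section 2.6 (Analysis Plan) of the protocol article gives the codes from 1 to 6 as "1 for strongly disagree, 2 for somewhat disagree, 3 for disagree, 4 for neutral, 5 for somewhat agree, 6 for agree", and the upper half in full as "5 for somewhat agree, 6 for agree, and 7 for strongly agree".

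For consensus, the seven codes are pooled: "the answering options are divided into disagreement (1 to 3), neutral (4), and agreement (5 to 7"). The threshold follows: "Consensus will be defined when a choice in the MCQ or Likert-scale question has at least 75% of the votes from panellists".

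For stability, the section says: "The stability of the responses will be analyzed from the second round onwards using the non-parametric Chi-square test or Kruskal–Wallis test". It does not say which test applies to Likert items, or whether the test runs on the seven codes or on the three groups. It adds that a p-"value of ≥0.05 will be interpreted as a lack of stability"; the Abstract defines stability by the same inequality, with the opposite meaning.

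Section 2.6 also promises the voting percentage for each answering option in the final results. Section 2.4.4 makes stability the condition for ending the rounds, and section 2.4.5 builds the panel statements on the last stable round.

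**The concern.** A 7-point agreement scale should grow in strength in both directions from neutral. The agreement side does. On the disagreement side, *somewhat disagree* stands next to *strongly disagree*, and the firmer *disagree* stands next to neutral. The upper half of the same scale shows what the lower half should look like.

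Two things could follow. First, a rank test on the seven codes would treat a move from *somewhat disagree* to *disagree* as a move towards neutral. Hardening opinion could then cancel out of the statistic, or softening could look like hardening, and the stability call could change. Second, if the form shows these labels, some panellists may answer by the word and others by the position on the scale. The counts for options 2 and 3 would then mix two meanings, and no recoding could separate them.

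**Working it through.** The plan states no figure on this point, so there is none to reproduce. The check asks which planned quantities change when labels 2 and 3 are exchanged.

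**Inputs from the article.** Pooling 1–3, 4 and 5–7; the 75% threshold; chi-square or Kruskal–Wallis; cut-off 0.05 (all section 2.6). Panel size: the Abstract says "For each part, a diverse panel of 30–40 experts will be selected", and section 2.3 says at least 35 to 40. The example uses 35 per round. **Assumed:** all response counts and distributions, that everyone answers by the word, and that the rounds are independent samples, as both tests treat them.

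**1. Consensus.** Codes 2 and 3 both lie in the 1–3 group, so exchanging them leaves the pooled count alone. The votes needed are 0.75 × 30 = 22.5, so 23; 0.75 × 35 = 26.25, so 27; and 0.75 × 40 = 30, in either order.

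**2. Constructed example, 35 per round.**

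| Answer | Round 1 | Round 2 | Total |
|---|---|---|---|
| strongly disagree | 3 | 8 | 11 |
| disagree | 6 | 12 | 18 |
| somewhat disagree | 21 | 10 | 31 |
| neutral | 3 | 3 | 6 |
| somewhat agree | 2 | 2 | 4 |

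Pooled disagreement is 30/35 = 85.7% in both rounds.

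*Chi-square.* With equal round sizes the statistic is the sum of (difference)² / total: 25/11 + 36/18 + 121/31 + 0 + 0 = 2.27 + 2.00 + 3.90 = 8.18 on 4 degrees of freedom, p = 0.085. The order of the categories does not enter.

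*Kruskal–Wallis on three groups.* The pooled counts are identical in the two rounds, so p = 1.0 in either order.

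*Kruskal–Wallis on seven codes.* With N = 70, H = [12/(N(N+1)) × (R1²/35 + R2²/35) − 3(N+1)] / C. The tie correction is C = 0.8916 in both orders, because the tie sizes are the same.

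- Mirrored order (disagree = 2, somewhat disagree = 3): mid-ranks are 6, 20.5, 45, 63.5 and 68.5. R1 = 3×6 + 6×20.5 + 21×45 + 3×63.5 + 2×68.5 = 1413.5, and R2 = 1071.5. H = 4.03/0.8916 = 4.52, **p = 0.033**.
- Printed order (somewhat disagree = 2, disagree = 3): mid-ranks are 6, 27, 51.5, 63.5 and 68.5. R1 = 3×6 + 21×27 + 6×51.5 + 3×63.5 + 2×68.5 = 1221.5, and R2 = 1263.5. H = 0.061/0.8916 = 0.068, **p = 0.79**.

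The two results fall on opposite sides of 0.05. Under the Abstract's rule the printed order gives stable and the mirrored order unstable; under section 2.6 the calls are reversed.

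**3. How often this might matter.** Simulation of seven-code Kruskal–Wallis, 2000 replicates per no-change setting and 4000 per shift setting, on assumed distributions:

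- No true change, n = 30, 35 and 40: p falls below 0.05 in 3.8–5.9% of items in the mirrored order and 4.3–5.6% with the codes swapped. The two orders give different calls in 0.4–0.6% of items for agreement-heavy panels and 5–7% for disagreement-heavy panels.
- Shift towards agreement (share in 5–7 rising from 60% to 80%), n = 35: 54% against 53%; calls differ in 3%.
- The comparable shift towards disagreement (share in 1–3 rising from 60% to 80%), n = 35: 54% against 27%; calls differ in about 30%.

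**The case against.** The strongest reply is that this is a typing slip with little reach. The article names two stability tests and does not assign Kruskal–Wallis to Likert items. Chi-square ignores category order, and any test on the three groups is blind to the swap. The consensus rule is untouched. The example is constructed so that all movement lies among disagreeing answers, and its pooled percentage passes 75% in both rounds. The questionnaire is not shown, and section 2.4.3 says only that it will use a 7-point Likert scale, so the form may already be in the right order.

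All of this stands, and it limits the size of the point. It does not remove it: the article sets out the full coding and sets it out wrongly, and seven-code Kruskal–Wallis is within what the plan permits. The movement in the example is also plausible for a statement the panel has already rejected, since most remaining change would then lie among codes 1–3.

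A reader might infer that the scale is not ordinal, or that the stability test is wrong. The article does not support either. One adjacent pair is transposed, while the three blocks remain in order. Kruskal–Wallis on the printed codes also keeps its level near 5% when nothing changes; what it loses is sensitivity, mainly to shifts among disagreeing answers. Nor can harm to medians or interquartile ranges be claimed, as section 2.6 specifies neither.

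**Conclusion.** The labels of codes 2 and 3 are transposed in section 2.6 and should be corrected. The consequence is confined to two places. One is a Kruskal–Wallis test on the seven codes, where p can cross 0.05 when answers move among the disagreeing options. The other, if the form carries the printed labels, is the meaning of the percentages reported for options 2 and 3.

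The size rests on assumed response patterns: almost no effect for agreement-heavy items, and differing calls in about 30% of items under one assumed shift towards disagreement. If panellists answered by position and ignored the words, the printed codes would rank their answers correctly. The data-capture risk depends on a questionnaire that cannot be seen here, so it is a reason to check the form and not evidence that the form is faulty.

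The opposite stability rules in the Abstract and section 2.6 are a separate and weightier contradiction. Until they are reconciled, neither p-value in the example can be called stable or unstable.

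**What to change.** In section 2.6, set 2 = disagree and 3 = somewhat disagree, leaving the other five labels as they are. Before round 1 opens, confirm that the questionnaire shows the same words against the same codes. State which stability test applies to Likert items and whether it uses seven codes or three groups, so that the reach of any label error is known.

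Section 2.8 says that the statements are still being formulated and that the first round is yet to come, so on the article's account the change costs two words and one look at the form. If a round has already been collected on the printed labels, recoding cannot separate answers given by word from answers given by position. In that case, report options 2 and 3 combined for that round and base stability on chi-square or Kruskal–Wallis over the three groups.
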